#### **Hypotheses:**

The alternative hypothesis for all endpoints is improvement with regard to the endpoint in the group of EPO-treatment. The null hypothesis for all endpoints is no improvement with regard to the endpoint in the group of EPO-treatment compared to the control group.

The study hypotheses are one-sided – however, the tests will be performed 2-sided yielding corresponding confidence intervals and accordingly information about the direction of a potential difference between control and treatment group.

The significance level alpha is 0.05.

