## 12.5 Determination of Sample Size

Information about effect size and standard deviation of the primary endpoint (IQ outcome at age of 5 years) can only be derived from one observational study presented by Neubauer AP et al. who investigated the effect of EPO-treatment of VLBW infants on composite IQ at 10 years.

Neubauer AP et al. included in their study all grades of IVH, also the lowest, IVH I°. However, diagnosis of IVH I° may be missed or even overestimated in very preterm infants. Neubauer AP et al. reported on no difference in infants without IVH regarding composite IQ at 10 years between EPO-treated and untreated, hence we decided to exclude infants with borderline diagnosis of IVH I° to avoid bias from misdiagnosis.

Neubauer et al. reported for the relevant group of children who suffered IVH an effect size between EPO-treated (IQ=90.3) vs. untreated (IQ=67.0) of 23, standard deviation (SD) 21,  $p < 0.01$ . Given that the vast majority of children will remain on their 5-year IQ trajectory, and there is good agreement between classification of cognitive abilities at 5 and 11 years of age, we used this continuous outcome parameter (effect size 23) for power analysis.

To determine the required sample size for the primary outcome we performed a power calculation for a 2-sample t-test assuming a significance level of  $\alpha=0.05$ ,  $SD=21$  of the outcome, and a 1:1 randomization. As result we get as required total sample size  $n=28$  (for both groups together), and  $n=38$  for a power ( $1-\beta$ ) of 0.8 and 0.9, respectively.

When assuming a smaller effect size of 10 (instead of 23), a SD of 15 (instead of 21 because IVH I° will be excluded in our study group to avoid misdiagnosis leading to a sample which is less heterogeneous with regard to the primary outcome) and a power of 0.8, the required total sample size is  $n=72$ .

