## 1 Background

EpoRepair is a randomized, double-blind, placebo-controlled, international multi-center study to investigate the effect of intravenously administered Recormon (recombinant erythropoietin, hereafter referred to as EPO) on the outcome of very preterm infants (born before 32 gestational weeks and/or 1500 g of birth weight) after intraventricular haemorrhage (grade II-IV, diagnosed by cranial ultrasound at a chronological age < 9 d). The aim is to evaluate whether EPO has the potential to ameliorate the neurodevelopmental sequelae of intraventricular haemorrhage. EPO as a verum is compared to NaCl 0.9 % as a placebo. Randomization was done 1:1, blockwise within each center (using a separate randomization list for each of the nine participating centers). The trial protocol was published by [[name] et al. \(2015\)](#).

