#### 2.2.1 Secondary outcomes at 5 years (like primary outcome)

- Normal overall developmental outcome (binary). Normal development at 5 years is defined as the combination of normal neurological evaluation, IQ > 84, and no neurodevelopmental deficits (all three conditions must be met).
- Mortality (binary)
- Developmental outcome categorized as normal, non-normal or dead (multinomial or binary: normal vs. non-normal or dead), combining the two outcomes just above into one

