### 3 Hypothesis

The alternative hypothesis for the primary endpoint is that EPO improves the intelligence quotient at 5 years of age compared to Placebo. The null hypothesis is no improvement with regard to the primary endpoint by EPO compared to Placebo.

Although the main study hypothesis is one-sided, we will apply two-sided tests. Estimates and confidence intervals will provide information about the direction of potential differences between the EPO and the Placebo arm.

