### 5.2.2 Analysis of secondary outcomes

Continuous secondary outcomes will be compared between treatment arms (EPO vs. Placebo) using a linear mixed-effects model with "treatment" as fixed explanatory factor and a random intercept per "center", like the primary outcome. We will report the resulting estimates of the EPO treatment effects together with 95 % confidence intervals and p-values (unadjusted and adjusted for multiple testing). The model assumptions will be checked by visual assessment of the residuals and either log-transformation of the outcome or the use of a generalized linear mixed-effects model (e.g. with Poisson error) may be considered in case of violations. For the outcome BSID-III at two years (combined score and subscores) we will add a sensitivity analysis to adjust for additional covariates, as specified as sensitivity analysis S1 for the primary outcome (Section 5.1). Moreover, the methods described for sensitivity analyses S3 and S4 may also be applied to continuous secondary outcomes.

Binary secondary outcomes will be compared between treatment arms (EPO vs. Placebo) using a generalized linear mixed-effects model with binomial error (referred to as logistic regression in the study protocol), again with "treatment" as fixed explanatory factor and a random intercept per "center". The resulting odds ratio (OR) estimates of the EPO treatment effect will be reported together with 95 % confidence intervals and p-values. Binary secondary outcomes from cUS (severe brain injury, posthaemorrhagic hydrocephalus grade  $> 1$ ) were measured three times: at baseline, 28 DOL and 36 weeks PMA. The measurement taken at baseline and the time of outcome measurement (28 DOL vs. 36 weeks PMA) will be used as additional fixed explanatory variables in the model. A random intercept per patient (nested in center) will be added to the model, to account for the non-independence of the repeated outcome measurements. In addition, we will assess the treatment  $\times$  time interaction. We will use the R package lme4 (Bates et al., 2015) to fit the models for binary outcomes and derive p-values using likelihood ratio tests.

Developmental outcome (normal, non-normal or dead) will be compared between treatment arms by a chi-squared test and will also be analyzed as binary outcome (normal vs. non-normal or dead) as described above.

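### SAP 5.2.2 tests normal / non-normal / dead with a plain chi-squared test that leaves out centre, the only named randomisation stratum, and yields no effect estimate or confidence interval

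*Combined protocol and SAP*

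**What the plan says.** SAP 2.2.1 lists, among the 5-year secondary outcomes, "Developmental outcome categorized as normal, non-normal or dead" and labels it multinomial or binary. A footnote says it was in neither version of the protocol and was added because a considerable share of the children die before age 5.

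SAP 5.2.2 gives the test: "Developmental outcome (normal, non-normal or dead) will be compared between treatment arms by a chi-squared test". The same sentence adds a binary version, normal against non-normal or dead, analysed like the other binary outcomes: a binomial mixed model with treatment fixed and a random intercept per centre, giving an odds ratio with 95% CI.

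On allocation, SAP 1 says: "Randomization was done 1:1, blockwise within each center". No other stratum is named. Protocol 12.3 sets out three levels of inference, the second of which adjusts for study centre. SAP 5 commits to estimates and 95% confidence intervals alongside every p-value.

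**The concern.** The SAP's models for continuous outcomes, binary outcomes and length of stay all carry centre, as a random intercept or a fixed effect. The three-level comparison does not, and SAP 9 does not list this among the deviations. When centres differ in outcome, a test that ignores the blocking factor tends to be conservative.

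A 2-df chi-squared p-value also shows no direction. Protocol 12.2 and SAP 3 ("Although the main study hypothesis is one-sided, we will apply two-sided tests") rely on estimates and intervals to show which arm does better. A significant result here could mean more normal children, fewer deaths or more deaths.

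This is the only planned test that handles death and development together at three levels, and it was added because of the deaths.

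**Working it through.** **Inputs from the documents.** 120 infants, 60 per arm (protocol synopsis); nine centres, 1:1, blocked by centre (SAP 1); "The significance level alpha is 0.05" (protocol 12.2), two-sided; about 15% in-hospital deaths (SAP 5.1); normal IQ 31% without and 49% with EPO (protocol 4.4). The last pair is only a proxy for normal development. Protocol 4.6 gives 24% and 62% from the same source, so the two should be reconciled.

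**Assumptions, not in the documents.** Unequal centre sizes (6 to 26), blocks of 4, and centre effects with SD 0, 0.3, 0.5 or 1 on the logit scale.

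**The plan's own figure.** Protocol 12.5: "When assuming a smaller effect size of 10 (instead of 23), a SD of 15", "and a power of 0.8, the required total sample size is" 72. Per arm, 2 × (1.960 + 0.842)² × 15² / 10² = 2 × 7.85 × 2.25 = 35.3, so 36, or 72 in total. It reproduces, but it concerns IQ. No power is stated for the three-level outcome.

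**Control distribution.** Normal 0.85 × 0.31 = 26.4%; non-normal 0.85 × 0.69 = 58.7%; dead 15%.

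**Tests compared.**
- Plain Pearson chi-squared on the 2 × 3 table, 2 df.
- Centre-stratified general association, 2 df. With x the indicators (normal, dead), U = Σ over centres of [sum of x on EPO − n₁ × centre mean of x], V = Σ n₁n₀ / [n(n − 1)] × Σ(x − mean)(x − mean)ᵀ, and Q = UᵀV⁻¹U.
- Centre-stratified rank test, 1 df, which imposes the order.

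**Rejection rates** (2,500 to 3,000 runs each, Monte Carlo error about 1 point):

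| Scenario | Centre SD | Plain 2 df | Stratified 2 df | Stratified rank |
|---|---|---|---|---|
| No effect | 0.5 | 5.5% | 5.5% | 5.6% |
| No effect | 1 | 3.8% | 4.7% | 5.0% |
| Common OR 1.98 | 0 | 38.6% | 38.0% | 48.1% |
| Common OR 1.98 | 0.5 | 35.1% | 36.7% | 47.5% |
| Common OR 1.98 | 1 | 29.4% | 35.7% | 45.8% |
| Common OR 2.5 | 0.5 | 59.5% | 61.7% | 71.5% |
| Survivors only, OR 2.14 | 0 | 34.5% | 34.5% | 26.8% |
| Survivors only, OR 2.14 | 0.5 | 32.1% | 33.8% | 27.3% |
| Survivors only, OR 3.0 | 0 | 67.8% | 67.6% | 50.2% |
| Survivors only, OR 3.0 | 0.5 | 62.4% | 63.6% | 47.4% |

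**Effect of centre alone** (stratified 2 df minus plain): 38.0 − 38.6 = −0.6 and 34.5 − 34.5 = 0 at SD 0; 1.6, 2.2, 1.7 and 1.2 at SD 0.5; 35.7 − 29.4 = 6.3 at SD 1. A repeat with centre sizes 30, 22, 18, 14, 10, 8, 8, 6 and 4 (4,000 runs) gave, at SD 1, 28.8% to 35.5% (common OR 1.98) and 23.9% to 28.2% (survivors only, OR 2.14), gains of 6.7 and 4.3, with null rejection 4.0% against 5.0%. Other runs of the same comparison gave gains of 5 to 8 points at SD 1 and null rejection of 3.6% against 4.8%.

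**Effect of imposing order** (rank minus plain). With a common odds ratio of 1.98: 48.1 − 38.6 = +9.5 at SD 0 and 47.5 − 35.1 = +12.4 at SD 0.5. With mortality unchanged: 26.8 − 34.5 = −7.7, 27.3 − 32.1 = −4.8, 50.2 − 67.8 = −17.6 and 47.4 − 62.4 = −15.0. In large-sample calculations with 20% deaths in both arms and 24% against 62% normal among survivors, the loss is 93.0 − 70.8 = 22.2 points with 60 per arm and 87.7 − 62.7 = 25.0 with 50 per arm.

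**The case against.** Several points favour the plan as written.

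- **A centre-adjusted analysis is already there.** The binary version adjusts for centre and gives an odds ratio with CI. Approximated by a stratified 1-df test, it beat the plain chi-squared test in every simulated scenario with an effect: 41.7% against 38.6% at common OR 1.98, and 40.7% against 34.5% for survivors only at OR 2.14, both at SD 0. Mortality and normal development are also listed separately and fall under the same binary model. This stands, and it limits the harm. It does not put centre or an estimate into the three-level comparison itself.
- **The protocol allows unadjusted comparisons.** Level 1 of protocol 12.3 is unadjusted and was written before this outcome existed. That is fair, but for the three-level version level 2 is then missing.
- **There is no false-positive risk.** The plain test is at worst conservative. This stands.
- **A 2-df test suits the outcome.** SAP 2.2.1 does not call it ordinal. If normal outcomes rose while deaths went from 15% to 25%, the plain chi-squared test would have 51% power, the rank test 4% and the binary version 23%. This stands, and argues for keeping 2 df.

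A reader might go further and infer that the plan throws away 9 to 12 points of power and should switch to an ordinal test. The documents do not support that. The figure comes mainly from the extra degree of freedom, not from centre: 80% power on 1 df becomes 70.9% on 2 df when all the signal lies in one ordered direction. It also needs EPO to shift death and development by the same odds ratio. At 2.14, the odds of death go from 0.15/0.85 = 0.176 to 0.176/2.14 = 0.082, so deaths fall from 15% to 7.6%. The documents do not claim a halving of mortality, and the earlier prophylactic trial's table in protocol 4.6 shows 5.9% deaths in each arm. With mortality unchanged, the ordinal test loses power.

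**Conclusion.** The point holds as a minor inconsistency in a late-added secondary outcome. The three-level test omits the randomisation stratum, unlike the SAP's other outcome models and the adjusted level of protocol 12.3, and it produces no estimate or interval despite SAP 5. These two facts need no simulation.

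The gain from stratifying is about 0 to 2 points of power at centre SD 0 to 0.5 and roughly 4 to 8 points at SD 1, where it also brings the null rejection rate from about 3.6–4.0% back to about 4.7–5.0%. The size rests on assumed centre SDs and centre sizes; the documents give neither. The primary IQ analysis is not affected.

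**What to change.** In SAP 5.2.2, replace the plain chi-squared test with a centre-stratified Cochran-Mantel-Haenszel general-association test (2 df, no order imposed), or with a multinomial model that includes centre. Report centre-adjusted odds ratios with 95% CIs for normal against non-normal and for death, next to the three-category table by arm. The first contrast conditions on survival and should be labelled so.

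With about 0.15 × 120 = 18 deaths over nine centres, fixed centre effects in a multinomial model could be unstable. The stratified test, or a random centre intercept, is the safer choice.

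The same edit should say whether the three-level or the binary version leads, which of them enters the Holm family, and how the test is combined over the 20 imputations: log odds ratios pool directly by Rubin's rules, a test statistic needs its own stated rule. An ordinal analysis should at most be supplementary, with the ranking of death below non-normal justified in advance.

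The cost is a few sentences in the SAP and an entry in SAP 9. No data collection or sample size changes, and in these simulations the stratified test never fell more than 1 point below the plain one, which is within simulation error.

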#### **Secondary endpoints:**

Normal overall developmental outcome at age of 5 years will be a secondary end point (binary variable). Normal development is determined in a neurological assessment at 5 years of age, including intelligence quotient (K-ABC or SON-R). Normal development at 5 years is defined as the composite outcome of: Normal neurological evaluation, IQ > 84, and no neurodevelopmental deficits.

Other secondary endpoints:

Advanced MRI at 40 weeks postmenstrual age (continuous outcome)

cUS at DOL 28 and at PMA 36 weeks (ordinal and continuous outcome)

BSID-III at two years of age (continuous outcome)

Mortality (binary outcome)

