The length of stay (LOS) in hospital will be analyzed as time to hospital discharge, using a competing risks model to account for the competing risk of in-hospital death (as recommended in [Brock et al., 2011](#)). We will use the R package survival ([Terry M. Therneau and Patricia M. Grambsch, 2000](#)) to fit a cause-specific proportional hazards model. For the sake of simplicity, we will include treatment and center as fixed effects (no random center effect).

We will once use the multiply imputed FAS and once the complete cases of the FAS for all secondary analyses.

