## 8 Handling of missing data and drop-outs

We will multiply impute missing outcome and covariate data due to death or loss to follow-up in the FAS. Multiple imputation will be performed by the R package mice ([van Buuren and Groothuis-Oudshoorn, 2011](#)), and will be applied separately at each stage of analysis (see Section 5). The imputation model will use all relevant baseline variables, the randomized treatment and outcome variables collected up to the time of analysis, potentially using correlations among outcomes for imputation in case the amount of missing data differs among outcomes. We will produce  $m=20$  imputations per missing value and analyze the 20 resulting complete data sets using Rubin's rules to pool the results.

While multiple imputation assumes missingness at random (MAR), missingness not at random can be investigated using the random indicator method proposed by [Jolani \(2012\)](#), mentioned also in [van Buuren \(2018\)](#). The latter will be used for sensitivity analysis S3.

In addition, a principal stratification approach suggested by [Hayden et al. \(2005\)](#) may be applied in order to estimate the "survivor average causal effect" (SACE), as proposed for sensitivity analysis S4.

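### For the 5-year outcome normal/non-normal/dead, complete cases keep every known death but drop unassessed survivors, and the imputation is not barred from recording a child known to be alive as dead

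*Combined protocol and SAP*

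**What the plan says.** SAP 2.2.1 lists among the 5-year secondary outcomes: "Developmental outcome categorized as normal, non-normal or dead". It is also to be analysed in binary form, normal against the other two categories combined. A footnote says it was added because a considerable share of the children die before age 5. 5-year mortality is listed separately as a binary outcome.

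SAP 5.2.2 gives the tests. For the three-level form: "Developmental outcome (normal, non-normal or dead) will be compared between treatment arms by a chi-squared test". The binary form follows the general rule: "Binary secondary outcomes will be compared between treatment arms (EPO vs. Placebo) using a generalized linear mixed-effects model with binomial error", with treatment as fixed factor and a random centre intercept. The same section closes with the missing-data rule: "We will once use the multiply imputed FAS and once the complete cases of the FAS for all secondary analyses".

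SAP 8 says of the imputation: "We will multiply impute missing outcome and covariate data due to death or loss to follow-up in the FAS". The imputation model takes baseline variables, treatment and the outcomes collected so far. There is no exception or constraint for vital status.

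Protocol 12.2 states what a survivor needs in order to be classified: "Normal development is determined in a neurological assessment at 5 years of age, including intelligence quotient (K-ABC or SON-R".

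Neither document says what makes a complete case for an outcome that has death as a category, or how the vital status of a child who does not attend is established.

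**The concern.** The three-level outcome is the SAP's safeguard against the survivor problem that it describes for IQ in SAP 5.1. That section warns of bias when losses differ between arms, but does not carry the warning over to the outcomes that include death.

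Death and survival reach the complete-case set by different routes. A child known to have died is in it. A living child is in it only if assessed at 5 years. Better tracing of vital status does not cure this for the three-level outcome, because a child known to be alive but untested still has no category. The dead share is then too high, and a difference in attendance between arms can look like a difference in deaths.

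The imputed version has the opposite fault. An untested child is simply missing on a variable with three levels, one of them death, so a draw of death is possible even for a child known to be alive. An outcome meant to guard against survivor bias would carry avoidable error of its own.

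**Working it through.** **Inputs.** Protocol 12.5: 120 enrolled, 15% early loss (death), then 20% loss up to 5 years. SAP 5.1: 20% loss expected in total, about 15% already dead in hospital. Allocation 1:1, so 60 per arm. Protocol 4.4: 31% and 49% with normal IQ in the observational study, used here only to illustrate the share of survivors who are normal. The attendance splits are assumptions; the documents give none by arm.

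**The plan's own chain.** 120 × 0.85 = 102, which the protocol rounds to 100; 100 × 0.80 = 80. This reproduces 120, 100, 80. The documents give no figure for 5-year mortality.

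**Dead share among complete cases.** With D deaths, S survivors and a the proportion of survivors assessed, the share is D / (D + aS). Assume that no lost child died unrecorded.

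| Loss figure | Deaths | Assessed survivors | Complete-case dead share | Share of all 120 |
|---|---|---|---|---|
| Protocol 12.5, unrounded | 18 | 0.8 × 102 = 81.6 | 18/99.6 = 18.1% | 15.0% |
| Protocol 12.5, rounded | 20 | 80 | 20/100 = 20.0% | 16.7% |
| SAP 5.1, 20% in total | 18 | 120 − 18 − 6 = 96 | 18/114 = 15.8% | 15.0% |

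The two sources conflict: the protocol's rounded chain loses 40 of 120 children, the SAP's wording 24 of 120.

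**Unequal attendance, no true effect.** With 9 deaths and 51 survivors per arm, the odds of dead versus assessed alive are 9 / (51a). The null odds ratio (EPO versus placebo) is therefore placebo attendance divided by EPO attendance.

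- 80/80%: odds ratio 1.00; only the levels are off.
- 85/75%: 0.75/0.85 = 0.88 (dead shares 17.2% and 19.0%).
- 90/70%: 0.70/0.90 = 0.78 (16.4% and 20.1%).

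**Binary form, normal versus non-normal-or-dead, at 90/70%.** If a proportion p of survivors is normal, the odds in an arm are 51ap / (9 + 51a(1 − p)).

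- p = 0.31: (14.23/40.67) / (11.07/33.63) = 1.06.
- p = 0.49: (22.49/32.41) / (17.49/27.21) = 1.08.

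**Three-level chi-squared test.** In 200,000 simulated trials per setting with no true effect, the false-positive rate was about 5.0% at 80/80, 5.4% at 85/75 and 6.9% at 90/70, for either value of p.

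**Imputation.** Vital status at 5 years was imputed by logistic regression on treatment and mortality at term, with data augmentation, in 2,000 simulated trials at 80/80 and 90/70% attendance. The mean number of lost survivors set to dead in one imputed data set was 0.55 to 0.59 with no deaths after term, and 0.95 to 0.98 with two such deaths.

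**The case against.** Four points can be made against this.

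*Mortality as such.* A reader might infer that complete-case mortality is necessarily biased in the same way. The documents do not support that. Mortality needs only vital status, and no passage says that a non-attender known to be alive is not a complete case. The protocol plans consistent contact with families (4.6), reimbursement of visit costs (7.5.1) and efforts to reach lost subjects (10.5). If every death is recorded and the others are counted as alive, the denominator is 120 and mortality is 15.0%. For mortality the gap is a missing rule, not a demonstrated bias.

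*Size.* Under the SAP's loss figure only about 6 survivors are lost. Even if all six came from one arm, the odds ratio would be 45/51 = 0.88; a split of 2 and 4 gives 47/49 = 0.96. Nothing in a double-blind trial points to a 90/70 split. The overstatement would also vanish if lost children had died as often as the complete cases: on the rounded chain, 4 of the 20 lost, since 24/120 = 20%. All of this stands, and limits the size.

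*Imputation.* A reader might infer that about four lost survivors per data set would be declared dead. That needs an imputation model without earlier mortality, whereas SAP 8 includes outcomes already collected, and mortality at term and at 2 years are among them. A small probability of death is also legitimate for a child whose status after last contact is unknown. It is not legitimate over a period when the child is known to be alive.

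*Status of the outcome.* It is one of many Holm-adjusted secondary outcomes. That argues for modest priority, but does not supply the missing constraint.

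**Conclusion.** The point holds for the three-level outcome and its binary form. It follows from the definitions: death is observable without a visit, and normal or non-normal is not. The dead share is overstated by about 3 percentage points under the protocol's attrition and by less than 1 under the SAP's, provided that no lost child died unrecorded. Treatment comparisons are distorted only if attendance differs between arms: clearly for dead versus assessed alive at the assumed splits, and slightly for normal versus the rest. The imputation fault is real but small, at most about one child per data set under the model that SAP 8 describes.

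The documents do not support the claim that the separate mortality analysis is biased as planned. What is missing there is a statement of how a child known to be alive is counted. This is an inexpensive improvement to secondary analyses and does not threaten the primary result.

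**What to change.** In SAP 5.2.2 and SAP 8:

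1. For normal/non-normal/dead and its binary form, hold vital status as observed. Impute only normal versus non-normal, and only among children known to be alive. Make this the reported analysis.
2. Drop the unweighted complete-case version of these outcomes, or label it supportive only.
3. For 2-year and 5-year mortality, count a child known from any contact to be alive at that age as alive, not missing. Do not impute death over a period when the child is known to be alive. State the rule for a child whose status after last contact is unknown.
4. Reconcile the loss figures in Protocol 12.5 and SAP 5.1, and show the results of this check under both until that is done.

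A time-to-death analysis censored at last contact is an option, not a necessity. It would need a date last known alive, which is not among the listed 2-year and 5-year items (Protocol 6.8 and 6.9); the date of death is listed only with the Visit 3 items (Protocol 6.6).

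The cost is SAP wording and a little more analysis work. The price in assumptions is that normal versus non-normal is missing at random among survivors, which is narrower than what SAP 8 assumes now.
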